## Abstract

**Background:**

Heart failure is a primary non-communicable disease in Latin America and the Caribbean, which significantly reduces patients’ quality of life. After diagnosis, emphasis is placed on cardiac rehabilitation and patient education regarding healthy lifestyles and habits. Interdisciplinary management is crucial in this process. However, lack of treatment adherence is a recurring issue in this population. In this context, technology allows us to address non-adherence to treatment. Its implementation helps overcome barriers and achieve treatment goals.

**Objective:**

To determine the effects of a cardiac telerehabilitation-mediated exercise program and telephone educational follow-up on functional capacity in patients with heart failure, compared with cardiac telerehabilitation and conventional outpatient cardiac rehabilitation.

**Methods:**

This article presents a SPIRIT-compliant protocol study of a three-arm, controlled, crossover clinical trial using participant blinding and simple sealed envelope block randomization.

**Conclusion:**

According to the literature review, this can be considered the first three-arm clinical trial in the telerehabilitation of patients with heart failure. The measurement and intervention instruments are comparable and adequate compared to other studies.

**Trial registration:**

ClinicalTrials.gov NCT05761639

## Introduction

Cardiovascular diseases (CVDs) are a significant public health problem worldwide and are considered the leading cause of preventable illness, disability, and mortality [1]. In Latin America and the Caribbean, CVDs are the leading cause of death from chronic non-communicable diseases. There are about 726,000 deaths per year, and these figures are increasing, being one of the leading causes of years lost in people [1]. Heart failure (HF) is one of the CVDs, so the incidence, prevalence, decline in quality of life, frequent hospitalizations, morbidity, and mortality associated with this disease are high, and chronic patients often present with disease-related decompensation [2,3].

In this regard, one of the best recommendations or Class I recommendations from scientific associations is cardiac rehabilitation (CR), which significantly improves adherence to treatment goals and survival in patients with HF [4,5]. CR programs improve quality of life and functionality and reduce long-term mortality by 20% to 30%. However, only 7.5% to 29% of patients are referred to and enrolled in a CR program, and only 40% to 55% of these patients can adhere to and complete treatment [6,7].

Lack of treatment adherence related to lifestyle changes and self-care is a factor that contributes to the occurrence of episodes of decompensation and hospitalization. This is reflected in the biomarkers and aerobic capacity measured through the 6-minute walk test [8]. Additionally, Poor health education, depressive symptoms, cognitive deficits, and multiple comorbidities may limit this low self-care capacity [6,9]. As a result, the low health literacy of HF patients translates into less knowledge about the disease, less self-care behaviors, deterioration of quality of life, and poor adherence to pharmacological and therapeutic treatment [9].

## Objective

The primary objective of this clinical trial is to assess the effects of a cardiac telerehabilitation-mediated exercise program combined with telephone educational follow-up on functional capacity in patients with HF. This will be compared to traditional outpatient cardiac rehabilitation.

The secondary objectives include evaluating the impact of the same telerehabilitation program on clinical variables, anxiety and depression, and health-related quality of life in HF patients, again in comparison to conventional outpatient cardiac rehabilitation. This study is designed as a three-arm randomized controlled trial, with blinding for the assessors, investigators, and data analysts.

## Materials and methods

### Study environment

This protocol study is a randomized controlled clinical trial of three-arm blinded to the assessor, the investigator and the information analyst. It has been registered on ClinicalTrials.gov (NCT05761639) and is currently collecting data, following the recommendations of the SPIRIT guide [9] (Fig 1). The study schedule is as follows: start was 15/10/2022, participant recruitment ended on 30/01/2025, and the estimated completion of the study is planned for 20/06/2025.

**Fig 1 pone.0327366.g001:**
[figure not shown]
SPIRIT schedule of enrolment, interventions, and assessments. 6MWT: the 6-minute walk test.

All patients will be informed about the study before recruitment. It will be conducted at the *Clínica de Occidente* SA in Cali, Colombia, where participants will be evaluated. Based on the evaluation, exercise prescriptions will be issued to guide patients during cardiac telerehabilitation and conventional outpatient cardiac rehabilitation.

### Ethics

This study adopted the ethical principles of the Declaration of Helsinki and Resolution 008430 of 1993 of the Ministry of Health and Social Security of Colombia. It was approved by the Ethics Committee of *the Clinica de Occidente S.A*. in June 2022 with code IYECDO-1598. All participants will be informed about the study, have their concerns addressed, and sign the informed consent form.

### Sample

The population will include patients with a diagnosis of HF who will be admitted to a cardiac rehabilitation program in the city of Santiago de Cali, Colombia. It should be noted that this study aims to compare quantitative variables. Studies that compare means use the standard deviation as a measure of variation, so the variable of interest will be the distance covered in meters in the 6-minute walk test (6MWT).

The hypothesis of this study proposes that the group receiving telerehabilitation, telephone follow-up, and education will achieve better results in patients’ aerobic capacity, compared to the other experimental groups.

There are no studies with similar characteristics with telephone follow-up to obtain a walking distance equal to that of the telerehabilitation group. This is because the groups are homogeneous at the beginning of the intervention but heterogeneous at the end of the intervention program; 378.5 ± 96.9 for the conventional outpatient cardiac rehabilitation group and 432 ± 83 for cardiac telerehabilitation).

In turn, 95% confidence is estimated, error α: 5% (0.05), error β: 20% (0.20), power: 1-β: 80%, giving n = 46 participants for each experimental group, which is increased by 12% for possible problems in the measurements or dropouts of the study participants, so that n = 52 will be required and a total of 156 patients with HF per experimental group at the end of the study.

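### The 80% power is derived from telerehabilitation versus conventional rehabilitation; the part of the hypothesis that sets Group 1 against Group 3 was not sized

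*Protocol article*

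**What the plan says.** The hypothesis in the Sample section is that "the group receiving telerehabilitation, telephone follow-up, and education will achieve better results in patients’ aerobic capacity, compared to the other experimental groups". In the labels of Table 1, Group 1 must therefore do better than Group 2 (conventional rehabilitation and education) and better than Group 3 (telerehabilitation and education). The abstract's objective names the same two comparators: "compared with cardiac telerehabilitation and conventional outpatient cardiac rehabilitation". The Objective section of the main text names one: "This will be compared to traditional outpatient cardiac rehabilitation".

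The inputs to the sample size are "378.5 ± 96.9 for the conventional outpatient cardiac rehabilitation group and 432 ± 83 for cardiac telerehabilitation". For the telephone component the section states: "There are no studies with similar characteristics with telephone follow-up to obtain a walking distance equal to that of the telerehabilitation group". It gives no expected distance for Group 1 and no expected difference between Groups 1 and 3. The result is stated as "error β: 20% (0.20), power: 1-β: 80%, giving n = 46 participants for each experimental group", then raised by 12% to 52.

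The section on data collection, management and analysis plans a one-way ANOVA with post hoc tests (Tukey or Dunnett's T3), and an ANCOVA adjusted for age, sex and other significant factors.

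**The concern.** The stated power follows closely on the hypothesis, so a reader will take it as the power for that hypothesis. The inputs, however, describe telerehabilitation and conventional rehabilitation. Table 1 shows that Groups 1 and 3 differ only in telephone follow-up, and Table 2 gives them one shared exercise prescription. Group 1 versus Group 3 is thus the only contrast that isolates the telephone calls, and it is the one with no assumed effect.

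Two things are at stake. A non-significant Group 1 versus Group 3 result could be read as evidence that telephone follow-up adds nothing, on the strength of an 80% power that does not apply to it. And because the Objective section and the hypothesis disagree on whether Group 3 is a comparator, the trial's success criterion is not settled: a result in which Group 1 beats Group 2 but not Group 3 would meet the one and fail the other.

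**Working it through.** **Inputs from the Sample section.** Conventional 378.5 m (SD 96.9); telerehabilitation 432 m (SD 83); α 0.05; power 80%; 46 per group. Sidedness is not stated. Two-sided reproduces 46; one-sided would give 36.

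**1. Reproducing the plan's figure.**
- Difference: 432 − 378.5 = 53.5 m.
- Pooled SD: √((96.9² + 83²)/2) = √((9389.61 + 6889)/2) = 90.2 m.
- Standardised difference: 53.5/90.2 = 0.593.
- A two-sided two-sample t-test at 0.05 with 80% power needs 45.6, so 46 per group. Power is 79.4% with 45 and 80.3% with 46.
- Inflation: 46 × 1.12 = 51.5, so 52.

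The stated 46 is this two-group comparison.

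**2. Group 1 versus Group 2.** Assume that telephone follow-up adds nothing, so that Group 1 also averages 432 m. Unadjusted power is then the same 80.3%. The Tukey critical value for three groups of 46 is q(0.95; 3, 135)/√2 = 2.370, against 1.987 for the unadjusted t-test (df 90). With it, power falls to 68% at SD 90.2. With the three-group SD √((2 × 83² + 96.9²)/3) = 87.9 it is about 71%.

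**3. Group 1 versus Group 3.** The documents give no difference, so a range is assumed. SD 83 is the article's telerehabilitation value and suits two telerehabilitation arms; SD 90.2 is the value behind the sample size. The standard error is SD × √(2/46), which is 17.31 m (SD 83) or 18.81 m (SD 90.2). Power is from the noncentral t distribution with noncentrality equal to the difference divided by the standard error.

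| Assumed gain from telephone follow-up | Unadjusted, SD 83 | Unadjusted, SD 90.2 | Tukey, SD 83 | Tukey, SD 90.2 |
|---|---|---|---|---|
| 10 m | 8% | 8% | 4% | 3% |
| 20 m | 21% | 18% | 12% | 10% |
| 30 m | 40% | 35% | 27% | 22% |
| 40 m | 63% | 56% | 48% | 41% |
| 53.5 m | 86% | 80% | 76% | 68% |

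The difference detectable with 80% power is a multiple of the standard error: 2.832 unadjusted, 3.216 with Tukey.
- SD 83: 2.832 × 17.31 = 49.0 m; Tukey 3.216 × 17.31 = 55.7 m.
- SD 90.2: 2.832 × 18.81 = 53.3 m; Tukey 3.216 × 18.81 = 60.5 m.
- With all 52 per arm retained: 46 to 50 m unadjusted.

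**4. Beating both groups, as hypothesised.** Group 2 was set at 378.5 m (SD 96.9), Group 3 at 432 m (SD 83) and Group 1 at 432 m plus the gain (SD 83), in 100,000 simulated trials. Unadjusted power to beat both was 8%, 21%, 41% and 64% for gains of 10, 20, 30 and 40 m. This is practically the Group 1 versus Group 3 power, so that contrast decides the joint claim.

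**The case against.** The strongest reply is that the unclear sentence on missing telephone studies can be read as using 432 m as a stand-in for Group 1. On that reading the calculation sizes Group 1 versus Group 2, which is the comparison in the Objective section. This stands in part. If Group 1 does no worse than telerehabilitation alone, that comparison keeps about 80% power or more at an unadjusted two-sided 0.05. It does not help Group 1 versus Group 3: the same reading sets those two means equal, and power is then only the error rate.

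A reader might go further and infer that the trial has almost no power for its hypothesis, or that a null Group 1 versus Group 3 result is to be expected. The documents support neither. Power depends on a gain that they do not state. It is very low near 10 m, low to moderate from 20 to 40 m, and above 80% once the gain passes about 49 to 53 m unadjusted.

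Nor does any passage credit a Group 1 versus Group 2 difference to the telephone calls alone. The Objective section describes a combined programme, and Group 1 versus Group 2 is a valid estimate of that package.

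Adjustment for baseline walking distance could raise power. With an assumed correlation of 0.7 and SD 83, Group 1 versus Group 3 would have 13%, 37% and 68% power at 10, 20 and 30 m. The article does not name baseline distance among the ANCOVA covariates, and 30 m would still fall short of 80%.

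**Conclusion.** The point holds for the match between the power statement and the hypothesis. The 46 per group and the 80% come from telerehabilitation versus conventional rehabilitation. They extend to Group 1 versus Group 2 under two conditions: Group 1 does at least as well as telerehabilitation alone, and no multiplicity adjustment is made (about 68% to 71% with Tukey if telephone follow-up adds nothing).

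They do not extend to Group 1 versus Group 3. There, 80% power requires the telephone calls alone to add roughly as much as the whole 53.5 m assumed for telerehabilitation over conventional care. This rests on 46 analysed per arm, an SD of 83 to 90.2 m, and no gain from baseline adjustment.

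On the choice of comparator, the abstract and the hypothesis agree with each other. The mismatch is that the Objective section leaves out telerehabilitation alone.

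**What to change.** 1. Restate the power sentence. The 80% applies to telerehabilitation-based care versus conventional rehabilitation, that is, to Group 1 versus Group 2 if telephone follow-up adds nothing, tested at an unadjusted two-sided 0.05. Group 1 versus Group 3 was not sized and has 80% power only for differences of about 49 to 53 m or more.
2. Make the abstract, the Objective section and the hypothesis name the same primary comparison.
3. Report Group 1 versus Group 3 with a 95% confidence interval, and state in advance that a non-significant result there is not evidence of no telephone benefit.

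These steps need no patients. Their price is a less favourable power statement for the telephone component.

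An optional further step is to make Group 1 versus Group 2 the single primary contrast and to test Group 1 versus Group 3 second, in fixed order. That would let the primary contrast be tested at the unadjusted level on which the 80% rests. It is more than rewording: it replaces the planned ANOVA and post hoc strategy and gives the Group 3 half of the hypothesis second place, and recruitment has already closed (30/01/2025, Study environment). If chosen, it should be recorded in a dated amendment before the data are unblinded or analysed.

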### Data collection, management, and analysis

The information obtained will be recorded in a Microsoft Office Excel 2010 database and exported for statistical analysis to the Statistical Software for Data Science (Stata) V.16. A description of the outcome variables and the population characteristics will be carried out to display the statistical behavior of these variables. Qualitative variables will be presented as frequencies and percentages, while quantitative variables will undergo the Kolmogorov-Smirnov test to determine whether their behavior is parametric or non-parametric.

If parametricity is confirmed, a Levene’s test for equality of variances will be conducted. Once parametricity is established, a paired t-test will be performed to compare pre- and post-intervention results for each group. For non-parametric behavior, the Wilcoxon test will be used, and variables will be presented as medians and interquartile ranges. Additionally, comparisons of the three experimental groups will be made at the start and end of the intervention. If the variables exhibit parametric behavior, a one-way ANOVA test will be used, followed by post hoc tests. For parametric variables with equal variances, the Tukey test will be applied (adjusting for unbalanced groups with Dunnett’s T3 test). If equal variances are not assumed, Dunnett’s T3 test will be used. For non-parametric variables, the Kruskal-Wallis test will be employed. A significance level of 95% will be considered, with a p-value < 0.05 regarded as statistically significant.

An analysis of covariance (ANCOVA) regression model will be used to evaluate the main effect of the outcome variable among the three experimental groups, adjusting for age, sex, and other potential confounding factors (those statistically significant at the 5% level).

A logistic regression model will be considered to analyze a binary outcome (e.g., adherence to recommendations provided through telephone follow-up), utilizing Akaike’s information criterion to select the best model based on its bias and variance.

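### The stated 80% power belongs to one unadjusted pairwise t-test, not the Tukey or Dunnett T3 comparisons planned (68% under Tukey at 46 per arm), and the trial total of 156 is labelled as a per-arm number

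*Protocol article*

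**What the plan says.** The Sample section of the protocol article takes the 6-minute walk distance as the sizing variable and rests on one pair of end-of-programme values: "378.5 ± 96.9 for the conventional outpatient cardiac rehabilitation group and 432 ± 83 for cardiac telerehabilitation". With α of 5% and power of 80% it states "giving n = 46 participants for each experimental group". It then raises this by 12% for measurement problems and dropout and ends with "n = 52 will be required and a total of 156 patients with HF per experimental group at the end of the study". Nothing in the section allows for more than one comparison, and sidedness is not stated. The hypothesis in the same section sets the telerehabilitation, education and telephone arm against both other arms.

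The section on data collection, management and analysis plans a one-way ANOVA across the three arms, followed by post hoc tests: "For parametric variables with equal variances, the Tukey test will be applied", with Dunnett's T3 where groups are unbalanced or variances differ. It also plans an ANCOVA across the three arms, adjusted for age, sex and other confounders chosen by statistical significance. The baseline walk distance is not named as a covariate.

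**The concern.** The power statement and the planned analysis describe different tests. A trial sized for one comparison at an unadjusted 5% loses power when each pairwise comparison must clear a stricter, multiplicity-adjusted threshold. A reader who relies on the 80% would then read a non-significant pairwise result as stronger evidence against a 53.5 m difference than it is.

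The last sentence also gives two incompatible per-arm targets, 52 and 156. It attaches the larger one to the end of the study, although it already contains the loss allowance. Recruitment ended on 30/01/2025 according to the article, so the number achieved will be compared with this sentence. Read literally, it asks for 3 × 156 = 468 patients.

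**Working it through.** **Inputs** (all from the Sample section unless noted)

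- Means 378.5 m and 432 m; difference 432 − 378.5 = 53.5 m.
- SDs 96.9 m and 83 m; pooled SD = √((96.9² + 83²)/2) = √(16278.61/2) = 90.2 m.
- Standardised difference d = 53.5/90.2 = 0.593.
- α = 0.05, power 80%. Two-sided is assumed because it reproduces the stated size; one-sided gives 36.
- Three arms of equal size; Tukey as the pairwise test (analysis section).

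**Step 1: reproduce the plan's 46.** The normal approximation is n = 2 × [SD × (1.960 + 0.842)/53.5]² = 44.6, so 45. The two-sample t-test has power 79.4% at 45 and 80.3% at 46, so it needs 46. The stated figure is therefore a single, unadjusted, two-sided two-sample t-test.

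**Step 2: reproduce 52 and 156.** 46 × 1.12 = 51.5, so 52. 3 × 52 = 156. Hence 52 is the per-arm figure and 156 the trial total. Both include the allowance for loss, so both are numbers to randomise.

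**Step 3: power under the planned Tukey test.** For one pair among three arms of n:

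- critical value c = q(0.95; 3, df)/√2, with df = 3(n − 1);
- non-centrality λ = d × √(n/2);
- power from the non-central t distribution with df and λ, compared with ±c.

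| Evaluable per arm | λ | c (Tukey) | Power, Tukey | Power, one unadjusted t-test |
|---|---|---|---|---|
| 46 | 2.84 | 2.370 | 68.2% | 80.3% |
| 52 | 3.02 | 2.367 | 74.4% | 85.0% |
| 59 | 3.22 | 2.364 | 80.3% | not needed |

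At 58 per arm Tukey power is 79.6%, so 59 is the smallest size that reaches 80%. A Bonferroni t-test at 0.05/3 gives a similar picture: 65.7% at 46 and 72.1% at 52. Dunnett's T3 was not computed.

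**Step 4: what baseline adjustment would have to deliver.** Adjusting for a baseline value that correlates r with the final value multiplies the residual variance by about 1 − r². To make 46 patients do the work of 59, 1 − r² = 46/59 = 0.78, so r is about 0.47. With 52, 1 − r² = 52/59 = 0.88, so r is about 0.34. This is approximate. It takes the quoted SDs as unadjusted end-of-programme SDs and applies the same Tukey adjustment to the adjusted means. The article gives no value for r, so these are thresholds, not predictions.

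**The case against.** The best defence is that the article does not say the Tukey test decides the primary result. It also plans an omnibus ANOVA and an ANCOVA. If the telephone arm merely matched telerehabilitation at 432 m (an assumption), omnibus power would be 84% at 46 per arm and 88% at 52. If that arm lay midway at 405.25 m, it would be 71% and 77%. Further, the 53.5 m contrast is telerehabilitation against conventional care and leaves out the arm expected to do best. If that arm differed from conventional care by 60 m (again an assumption), Tukey power would be about 79% at 46 and 85% at 52.

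This limits the claim but does not remove it. An omnibus result does not say which arms differ, and the hypothesis is about particular arms. The more favourable figures need effects that the article does not state. For the only difference it does state, the planned pairwise test misses 80% even with no loss. The ANCOVA may recover precision, but as written it does not name the baseline walk distance, so no gain can be credited yet.

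On the label, it is fair to say that the words about a total and the adjacent 52 let a careful reader recover the meaning. It is a wording error, not a wrong calculation.

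Two stronger readings are tempting and not supported:

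- A reader might infer that the 12% allowance is miscalculated, since 46/0.88 = 52.3 would round to 53. The text says the number is increased by 12%, which 52 matches. The gap is one patient per arm, and unadjusted power at 45 is still 79.4%.
- A reader might set the 12% against the Introduction's remark that "only 40% to 55% of these patients can adhere to and complete treatment" and infer a collapse in power. That remark is background on rehabilitation programmes generally. It does not forecast missing 12-week walk tests in this trial, and the article nowhere restricts the analysis to programme completers.

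**Conclusion.** The point holds in two parts. First, the 80% power applies to one unadjusted two-sided comparison of 53.5 m. Under the planned Tukey comparisons it is 68% with 46 evaluable per arm and 74% with all 52, a shortfall of about 12 and 6 percentage points against the stated figure. This rests on the article's own means and SDs, equal variances, a two-sided 5% level, and Tukey as the test by which pairs are judged. Second, 156 is wrongly described as a per-arm number at the end of the study; it is the total to be randomised across three arms of 52.

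It does not follow that the sample-size figures are wrong as a set. 46, 52 and 156 (as a total) all reproduce from the stated inputs. The errors lie in what the 80% is said to cover and in the label on 156. Both should be corrected, and neither calls for a larger trial.

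**What to change.** Replace the closing sentence of the Sample section with wording such as:

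> 52 patients per arm, 156 randomised in total. With about 46 evaluable per arm, power is 80% for one unadjusted two-sided 5% comparison of 53.5 m (SD 90.2 m), and about 68% per pair under Tukey adjustment with equal variances (74% if all 52 are evaluable).

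In the analysis section, name the baseline 6-minute walk distance as a covariate in the planned ANCOVA for that outcome, whatever its significance. It is measured in every patient before enrolment, so this needs no new data.

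Naming one primary contrast to be tested at 0.05 would align the analysis with the single comparison used for sizing. That is an option, not a required correction, and is credible only if done before outcome data are examined.

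The cost is a corrected paragraph, one added covariate and a less favourable stated power. No patients are added.
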